**1.7 Study Design.**

All patients included in the study will receive zoledronic acid every 4^th^ week for two years. Patients who after two years of treatment meet the eligibility criteria will be randomised (1:1) to stop treatment with zoledronic acid and enter the observation arm (treatment arm A) or to receive zoledronic every 4^th^ week up to a total period of four years (treatment arm B). Randomisations will be conducted when the patient has been in the study for two years (+/- 1 month). The randomisation procedure will be stratified according to previous autologous stem cell treatment, presence or absence of bone disease at diagnosis, previous treatment with bortezomib.

Treatment with zoledronic acid can be started before initial bone imaging has been conducted. Blood samples for measurement of fasting serum bone markers however must be collected prior to zoledronic acid treatment and anti-myeloma treatment.

Acquiring source data and planned visits.

Inclusion:

The patient must meet the specified inclusion and exclusion criteria’s.

Bone imaging must not be done more that two months prior to inclusion and should be done no more than one month after inclusion.

Fasting serum bone markers must be collected prior to treatment with zoledronic acid as well as prior to treatment with anti-myeloma treatment. Serum bone markers do not need to be collected prior to bone imaging. In case of a more than two weeks delay between initial bone marker measurements and actual infusion of zoledronic acid, new serum markers should be collected prior to the first infusion.

QoL questionnaire QLQ-C30 and MY20 should be completed no more that 2 weeks after inclusion.

Infusion with zoledronic acid should be initiated as soon as possible. However, allowing time to dental examination and possible tooth extraction and healing, zoledronic acid infusions should not be initiated later than three months after initiation of anti-myeloma treatment. Dental examination will be conducted according to local guidelines.

Planned visits year 0-2:

Bone imaging will be conducted after one year and after two years of treatment. Both time-points can be moved +/- 1 month. Bone imaging should be conducted using both conventional radiography and low-dose CT. Sites however may participate in the study without conducting both conventional radiography and low-dose CT. In that case, the chosen modality must be used consistently throughout the entire study period.

Fasting serum bone markers will be collected bi–annually. All time-points can be moved +/- 2 weeks.

Measurements of creatinine and calcium may be conducted up till 2 weeks before the visit

QoL questionnaire QLQ-C30 and MY20 will be used bi-annularly. All time-points can be moved +/- 2 weeks.

Infusion with zoledronic acid should be given ever 4^th^ week (+/- 1 week). Infusion can be delayed for up to 2 months e.g. due to temporarily impaired renal function (meaning a three month pause between two infusion is allowed). If infusions cannot be given within this time period the patient will be excluded from the study. If infusions are delayed for a significant period, it is the time passed and not the number of infusions that is relevant as to when stratification occurs.

Randomisation:

At year 2 patients will be randomised to A) stop treatment with zoledronic acid or to B) continue treatment with monthly infusions of zoledronic acid for another 2 years period (4 years in total). Randomisation is allowed to be moved -1months/+2months. The randomisation procedure will be stratified according to previous autologous stem cell treatment, presence or absence of bone disease at diagnosis, and previous treatment with bortezomib. Randomisation will take place at The Hematological Research Unit, Odense University Hospital, Denmark. For further details see appendix 6 (SOP for randomisation).

Planned visits, year 2-4:

Bone imaging will be conducted after 2½ years, after 3 years, after 3½ years, and after 4 years. All time-points can be moved +/- 1 month. In case of myeloma relapse requiring active treatment, new bone imaging should be conducted within a one-month time frame of initiation of new anti-myeloma treatment. If bone imaging has been conducted as part of relapse evaluation no less than three month prior to routine bone imaging time point,no new bone imaging need to be conducted. If any bone imaging, conducted from year 2 to 4, reveals PBD in patients not receiving zoledronic acid and the treating physician find it necessary to reinitiate treatment with zoledronic acid, the patient will be excluded from the study. In that case, fasting serum bone markers should be measured prior to re-initiation of zoledronic acid treatment. If bone imaging, conducted as part of a myeloma relapse evaluation in patients not receiving zoledronic acid, results in “no PBD”, treatment with zoledronic acid should *not* be re-initiated.

Bone imaging should be conducted using both conventional radiography and low-dose CT. Sites however may participate in the study without conducting both conventional radiography and low-dose CT. In this case, the chosen modality must be used consistently throughout the entire study period.

Fasting serum bone markers should be collected every fourth week (+/- 1 week) throughout this period. Serum samples do not need to be collected at the exact date of zoledronic acid infusion but can be collected up to two weeks prior to infusion; serum samples however must not be collected after zoledronic acid infusion. Measurements of creatinine and calcium may be conducted up till 2 weeks before the visit

QoL questionnaire QLQ-C30 and MY20 will be used every 3^rd^ month: after 27, 30, 33, 36, 39, 42, 45, and after 48 months. All time-points can be moved -2 weeks.

Infusion with zoledronic acid in the treatment arm should be given ever 4^th^ week (+/- 1 week). Infusion can be delayed for up to 2 months e.g. due to temporarily impaired renal function (meaning a three month pause between two infusion is allowed). If infusions cannot be given within this time period the patient will be excluded from the study.

For specific instructions concerning conventional radiography and low-dose CT, see appendix 2

For specific instructions concerning serum bone makers, see appendix 3

Amendment:

Patients who are included after 23-25 zoledronic acid infusions outside protocol will move directly to randomisation. The randomisation procedure will be stratified according to previous autologous stem cell treatment, presence or absence of bone disease at diagnosis, and previous treatment with bortezomib. Randomisation will take place at The Hematological Research Unit, Odense University Hospital, Denmark. For further details see appendix 6 (SOP for randomisation).

Acquiring source data (amendment):

Bone imaging must not be done more than two months prior to inclusion and should be done no more than one month after inclusion.

Fasting serum bone markers must be collected no more that 2 weeks after inclusion.

QoL questionnaire QLQ-C30 and MY20 should be completed no more that 2 weeks after inclusion.

Investigation according to local guideline for any pre-existing BON must be conducted before inclusion in the protocol amendment

Planned visits, year 2-4: (amendment)

No changes compared to original description.

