Zoledronic acid is administrated to the patients in order to minimise the risk of PBD. In this study, we want to evaluate if the potential benefit of prolonged zoledronic acid treatment outweigh the increased risk of BON. To minimise the risk of undetected PBD we will from year 2 to 4 conduct regular bone imaging every 3 month. Furthermore, it is mandatory to conduct bone imaging in case of progressive myeloma disease requiring treatment. To further improve the safety of the patients we have invented a less rigours event definition (PDB) compared to the more strict definition (sPBD) where the progression have to be symptomatic to be calculated as an event. All cases of sPBD will be reported annually to the sponsor.

Radiation exposure:

The following text applies to patients in which evaluation of bone disease is conducted with both conventional radiography and low-dose CT, thus it is the patients who receive the highest radiation dose.

Scheduled bone imaging will be conducted seven times during the four years period. Perhaps one extra bone imaging will be conducted in case of relapse from year 2-4. This equals a total radiation dose of 45.5-52 mSv. A patient not included in the study would probably within the same time frame have approximately three conventional radiography and 1-2 low dose CT conducted, equal to a total radiation dose of 11.3-15.4mSv. The patients will over a four years period receive an excess radiation dose of 33.2-36.6, which is equivalent to the dose received from 1.5 conventional CT. The additional bone imaging will not only be conducted for scientific reasons, but also to make sure no serious progressive bone disease occurs when the patient is not receiving zoledronic acid.

Drug administration and renal function

Four mg of zoledronic acid will be administered intravenously at the hospital every fourth week (+/- 1 week) according to local instructions, for either two or four years.

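### The relapse-scan waiver in section 1.7 sets three months as a minimum age, so read literally an old relapse scan replaces a routine year 2-4 scan and a recent one does not

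*Protocol*

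**What the plan says.** Section 1.7 (Planned visits, year 2-4) fixes the calendar: "Bone imaging will be conducted after 2½ years, after 3 years, after 3½ years, and after 4 years". Each date may shift by one month either way. For a relapse that has to be treated, the section adds a scan: "new bone imaging should be conducted within a one-month time frame of initiation of new anti-myeloma treatment".

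The waiver follows. Its condition is that "bone imaging has been conducted as part of relapse evaluation no less than three month prior to routine bone imaging time point". Where that condition is met, the section says that "no new bone imaging need to be conducted". No upper limit on the age of the relapse scan is given. The amendment text leaves the year 2-4 visits unchanged.

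Section 1.8 (Risk of PBD) gives the purpose, and a different interval: "To minimise the risk of undetected PBD we will from year 2 to 4 conduct regular bone imaging every 3 month". The radiation paragraph of the same section counts seven scheduled scans over four years, with perhaps one more at relapse, for 45.5-52 mSv.

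The primary endpoint (section 1.5) is time to PBD from year 2 to year 4. Section 1.12 has a similar construction: for imaging after withdrawal it sets one month as the shortest delay, where a longest delay would be expected.

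**The concern.** A rule that lets one scan stand in for another normally requires the substitute to be recent. Here the limit runs the other way. The routine scan may be dropped when the last image is old, and must be repeated when the last image is a few weeks old. That serves neither early detection nor radiation sparing, the two aims that section 1.14 says the imaging balances.

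The lytic part of PBD is seen only on imaging, so its date is the date of a scan. The patients affected are those who relapsed, whose relapse scan showed no PBD and who stay in follow-up. In the observation arm, section 1.7 says that such patients should not restart zoledronic acid on that finding, so the next scan matters for them. A skipped scan dates their PBD later, and a skipped year-4 scan can leave it unseen within the endpoint window. Section 1.13 measures bone markers over the six months before PBD, and late dating would shift that window too.

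**Working it through.** **Calendar check.** Scans at months 0, 12, 24, 30, 36, 42 and 48 make 7. The dose per occasion is 4.1 + 2.4 = 6.5 mSv (section 1.3). 7 × 6.5 = 45.5 and 8 × 6.5 = 52 mSv, as stated in section 1.8. Three-monthly imaging from month 24 would give 3 + 8 = 11 scans, or 71.5 mSv. The radiation figures therefore match the six-monthly calendar of section 1.7, which is used below.

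**Gap after a relapse scan at month t.** Let R be the next routine date, and apply the waiver to that scan only. If it is waived, the next scan falls at R + 6, so the gap is (R − t) + 6. If R = 48, the last image is R − t months old when the window closes.

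- As written (R − t ≥ 3): R − t runs from 3 to 6, so the gap is 9-12 months, or the last image is 3-6 months old at month 48.
- As a maximum (R − t ≤ 3): R − t runs from 0 to 3, so the gap is 6-9 months, or the last image is 0-3 months old.

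A late following scan (+1 month) extends the longest gap from 12 to 13 months as written.

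| Relapse scan at month | As written | As a maximum |
| --- | --- | --- |
| 31 | month 36 waived, next at 42 (11 months) | month 36 done (5 months) |
| 35 | month 36 done (1 month) | month 36 waived, next at 42 (7 months) |
| 43 | month 48 waived, last image 5 months old | month 48 done |
| 47 | month 48 done | month 48 waived, last image 1 month old |

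**Without the next-scan-only restriction.** The sentence does not contain that restriction. A relapse scan at month 25 is at least three months before months 30, 36, 42 and 48, so on the fullest literal reading it waives all four. The 9-12 months is therefore not a ceiling.

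**How many patients.** The protocol gives no relapse rate. Assume a constant rate r of 0.15, 0.25 or 0.35 per year from month 24, with the relapse scan at relapse, every available waiver used, and no deaths, exclusions or earlier PBD. The waiver is open in the first three months of each six-month interval:

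P(routine scan waived) = (1 − e^(−0.25r)) × (1 − e^(−2r)) / (1 − e^(−0.5r))

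- r = 0.15: 0.0368 × 0.2592 / 0.0723 = 13.2%
- r = 0.25: 0.0606 × 0.3935 / 0.1175 = 20.3%
- r = 0.35: 0.0838 × 0.5034 / 0.1605 = 26.3%

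P(year-4 scan waived) = e^(−1.5r) × (1 − e^(−0.25r))

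- r = 0.15: 0.7985 × 0.0368 = 2.9%
- r = 0.25: 0.6873 × 0.0606 = 4.2%
- r = 0.35: 0.5916 × 0.0838 = 5.0%

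**What a maximum would change.** It opens the waiver in the other half of each interval. The share is 1 − e^(−2r) less the share above: 25.9 − 13.2 = 12.7%, 39.3 − 20.3 = 19.0%, and 50.3 − 26.3 = 24.0%. About as many scans could be waived; what changes is which ones. The scans dropped would be those with a recent image behind them.

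**The case against.** The strongest reply is that this is a language slip, not a design rule, and that sites will read it sensibly. Section 1.12 shows the same construction, while sections 1.6 and 1.7 state other imaging limits correctly as maxima. That is probably right about intent. It does not remove the problem, because the sentence is the operative instruction and nothing in the text at hand overrides it. The flowchart and imaging manual (Appendices 1 and 3) are not shown and might.

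Several points limit the consequences, and they stand:

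- The waiver is permissive. The scan need not be done, but it may be.
- The relapse scan is itself an added image at a time of raised risk. With one waiver used, the number of scans is unchanged.
- Patients whose relapse scan shows PBD, or who had PBD earlier, already have the event. Those who have died or left the study lose nothing either.
- Hypercalcaemia counts as PBD and calcium is measured monthly. Symptomatic fractures can also present between scans.
- If the three-monthly interval in section 1.8 applied, a relapse scan would almost never be three months before the next nominal date, and the next-scan-only problem would largely vanish.

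A reader might infer that relapsed patients as a rule go 9-12 months without imaging, or that the comparison between arms is biased. The documents support neither. The first would need every site to use the waiver literally. The second would need relapse or waiver use to differ by arm, and the protocol gives no relapse rate and no reason to expect a particular direction.

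**Conclusion.** The point holds as a defect of wording in a rule that governs how the primary endpoint is ascertained. Followed as written for the next scan only, it allows 9-12 months to the next scan, or a last image 3-6 months old at month 48, in event-free patients with a relapse scan showing no PBD. A maximum of three months would allow 6-9 and 0-3 months. This improves matters but does not restore six-monthly spacing. Because the text has no upper age limit, longer gaps are possible.

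The shares of 13, 20 or 26% (any routine scan) and 3, 4 or 5% (year-4 scan) are upper bounds. They rest on assumed relapse rates, full use of the waiver and the six-monthly calendar. Confidence is high on the wording and lower on how much it affects the data. Unequal ascertainment between arms is a possibility only. The sentence should be corrected because following it literally gives worse endpoint data and the correction is cheap.

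**What to change.** 1. In section 1.7, state the limit as a maximum age, in line with the imaging purpose in section 1.8, so that only a recent relapse scan can stand in for a routine one. Say that it replaces that one scan only.
2. State that a relapse scan does not replace the year-4 endpoint scan unless it falls within that scan's window of plus or minus one month.
3. Correct the parallel wording on imaging after withdrawal in section 1.12 in the same edit.
4. Reconcile the six-monthly calendar in section 1.7 with the three-monthly interval in section 1.8, and check that the radiation figures follow from whichever is meant.

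The cost is a few sentences. A few patients keep a scan that the present wording would let them skip, but it is already counted in the 45.5-52 mSv. Others are spared a repeat within weeks of a relapse scan.

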Amendment: After the Nordic Myeloma Study Group began working on this protocol, zoledronic acid is becoming the preferred bisphosphonate outside clinical trials in the Nordic Region. As a consequence there are now patients outside clinical trials who have received two years of zoledronic acid treatment. These patients may be included in the trial when they have received 24 infusion with zoledronic acid. They will be randomised at the time of inclusion.

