**1.5 Study Objectives.**

Endpoint definitions.

PBD:

≥ 25% progression in size of existing osteolytic lesions (a total growth of at least 10 mm is required in the longest dimension) or vertebral fractures, new osteolytic lesions (at least 10 mm in the longest dimension) or fractures, spontaneous factures, new vertebral compression, new osteolytic lesions needing irradiation therapy or surgery, hypercalcaemia caused by the myeloma (S-Ca-ion > 1,40 mmol/L or in case S-Ca-ion is not measured: S-Calcium adjusted for S-albumin > 2,75 mmol/L), measured in at least two consecutive blood samples.

PBD can be diagnosed on either conventional radiography or low-dose CT. The development however must be defined by comparing the same modality over time. The modality used at the time of randomisation (year 2) will be used as baseline value.

sPBD:

Spontaneous factures, new vertebral compression, new osteolytic lesions needing irradiation therapy or surgery, hypercalcaemia caused by the myeloma (S-Ca-ion > 1,40 mmol/L or in case S-Ca-ion is not measured S-Calcium adjusted for S-albumin > 2,75 mmol/L), measured in at least two consecutive blood samples).

sPBD can be diagnosed on either conventional radiography or low-dose CT. The development however must be defined by comparing the same modality over time. The modality used at the time of randomisation (year 2) will be used as baseline value.

Bone healing:

≥ 25% reduction in the size of osteolytic lesions (a reduction of at least 10 mm in the longest dimension is required), increased sclerosis in the edge of existing lesions, or healing of existing lesions. Bone healing can be diagnosed on either conventional radiography or low-dose CT. The development however must be defined by comparing the same modality over time.

The modality used at the time of randomisation (year 2) will be used as baseline value.

BON:

To diagnose BON the following criteria must be fulfilled

1: Current or previous treatment with a bisphosphonate AND

2: Exposed, necrotic bone in the maxillofacial region that has persisted for more that 8 weeks AND

3: No history of radiation therapy to the jaws [[29](#_ENREF_29)]

No bone disease / Bone disease:

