-The patient should have received at least 12 infusions with zoledronic acid in the previous two years period. If a patient has received less than 12 infusions in the previous two years he / she it not eligible for randomisation and should leave the study.

Patients who fail to be included in the study will be treated according to the local standards. Patients who will be excluded from the study because they fail to meet the criteria for randomisation (at year two) will likewise be treated according to the local standards. Radiological data from these patients will still be used to evaluate secondary endpoints in the study. No additional protocol related follow-up is planned once the patients leaves the protocol either timely or untimely. Future treatment will be decided by the local hospital and the patient.

Amendment: Patients may be included when they have received two years of zoledronic acid treatment outside clinical trials. They will proceed directly to randomisation

Inclusion criteria (amendment)

- Earlier diagnosed with symptomatic Multiple Myeloma according to the IMWG criteria, regardless of bone disease status

-Signed Informed Consent

-Age ≥ 18 years

-Remaining life expectancy ≥ 1 years

-Received 23-25 monthly infusions with zoledronic acid

-Any concurrent anti-myeloma treatment are allowed

Exclusion criteria (amendment) :

-Severely reduced renal function (creatinine clearance <30 mL/min despite fluid replacement)

-Known concurrent malignancy, excluding skin cancer

-Known hypersensitivity to zoledronic acid

-Pregnant or lactating women

-Women of childbearing potential or men engaging in sexual activity with a woman of childbearing potential who refuse to use contraception (safe methods of contraception are considered to be: combined (estrogen and progestogen containing) hormonal contraception associated with inhibition of ovulation, progestogen-only hormonal contraception associated with inhibition of ovulation, intrauterine device (IUD), intrauterine hormone-releasing system ( IUS) bilateral tubal occlusion, vasectomy, and sexual abstinence. Contraception must be used until 56 days after the last infusion).

- Progressive bone disease diagnosed using bone imaging, less than or equal to three month prior to the randomization

- Developed BON during earlier zoledronic acid treatment

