**1.15 Privacy of Personal Data and Data Handling**

Each patient will be assigned a personal identification number on inclusion. The data will be archived in accordance with GCP rules for 5 years in Denmark and Norway and for 10 years in Sweden following completion of the study. The collection and processing of personal data from patients enrolled in this study will be limited to

those data that are necessary to investigate the efficacy, safety, quality, and utility of the study drugs

used in this study.

The data will be recorded on case report forms (CRF). Patients will receive a protocol number for the CRF. A patient log which may pair the protocol number with the civic registration numbers will be kept under lock and key at the sponsor’s research facility. Since this is not a blinded study decoding of the patients will probably not be necessary. However if a situation arises where it is deemed in the best interest of the patient to break to code, this will have to be decided by the national investigator or the sponsor.

Bone markers will not be measured locally. Instead serum samples collected during the study will be stored locally and then later sent to The Haematological Research Unit in Odense, Denmark. Bone markers measured bi-annually will be analysed for all patients. As stated in section 1.13 32 cases and 32 controls will be selected and monthly bone markers will be analysed 6 months retrospectively in these patients. The serum samples are collected for this specific purpose and no in order to created a research biobank. For further details on the bone markers see appendix 2.

Radiological data will be mailed to The Haematological Research Unit in Odense, Denmark. They will be kept there for later review, as specified in appendix 3.

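### Amendment-route patients are randomised at inclusion, yet their baseline imaging may follow by up to a month, so eligibility and the primary-endpoint baseline can be set with the open-label arm known

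*Protocol*

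**What the plan says.** Three places in the Protocol put randomisation at entry for amendment patients. Section 1.4: "They will be randomised at the time of inclusion". Section 1.6: "They will proceed directly to randomisation". Section 1.7: they "will move directly to randomisation".

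Under the amendment's source-data heading, section 1.7 then sets the imaging window: "Bone imaging must not be done more than two months prior to inclusion and should be done no more than one month after inclusion". It also says "QoL questionnaire QLQ-C30 and MY20 should be completed no more that 2 weeks after inclusion" and gives fasting bone markers the same two weeks. In the same list, the check for pre-existing osteonecrosis of the jaw must precede inclusion.

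Two other rules are tied to randomisation:

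- The amendment's exclusion criteria in 1.6 include "Progressive bone disease diagnosed using bone imaging, less than or equal to three month prior to the randomization".
- The PBD definition in 1.5 states "The modality used at the time of randomisation (year 2) will be used as baseline value". This literally names the modality. I read it as making the imaging at randomisation the reference for later comparison.

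The arms are open. Section 1.15: "Since this is not a blinded study decoding of the patients will probably not be necessary". Section 1.13 analyses patients per protocol and by treatment actually received.

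**The concern.** For newly diagnosed patients the same imaging window is harmless, because inclusion precedes randomisation by two years. The wording appears to have been carried over to a route where the two coincide, so that after inclusion means after allocation.

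The stake is the order of three steps: eligibility, baseline, allocation. If the scan comes last, whoever reads it or acts on it may know the arm. That scan decides whether recent PBD should have kept the patient out, and it is the reference for every later PBD judgement. The per-protocol analysis would not undo a removal made after allocation. Baseline quality of life, the reference for a between-arm secondary endpoint, may likewise be answered by a patient who knows whether treatment is stopping.

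**Working it through.** **1. Windows around randomisation, amendment route.** Inclusion equals randomisation, so imaging may fall from 2 months before to 1 month after allocation. The 1.6 exclusion looks at imaging in the 3 months before randomisation. A patient first imaged after allocation has no scan to which it can be applied. As worded, such a patient passes because nothing has been diagnosed.

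**2. Does another scan close the gap?** Section 1.3 gives 4.1 mSv for low-dose CT and 2.4 mSv for conventional radiography: 4.1 + 2.4 = 6.5 mSv per combined examination. Section 1.8 gives 45.5 mSv for the standard route: 45.5 / 6.5 = 7, matching the seven scheduled examinations stated there. For the amendment route it gives 32.5 mSv: 32.5 / 6.5 = 5. Four of these are the follow-up examinations at 2½, 3, 3½ and 4 years. One is left, so a single scan is budgeted as both eligibility check and baseline.

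**3. The plan's sample size.** Inputs from 1.13: 7.5% per year on drug, a risk reduction of 0.5 (read as 15% per year after stopping), one-sided 0.05, 80% power, 2 years.

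- Freedman events: (1.645 + 0.842)² × (1.5 / 0.5)² = 55.6, rounded up to 56.
- Two-year probabilities: 1 − exp(−0.15) = 13.9% and 1 − exp(−0.30) = 25.9%, mean 19.9%.
- Patients per group: 56 / 0.1992 / 2 = 140.5, within 3% of the stated 143.
- Included: 286 / 0.8 = 357.5, rounded up to 358, as stated.
- Expected two-year events with 143 per arm: 143 × (0.139 + 0.259) ≈ 57.

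**4. First-month events that a late baseline could absorb.** Upper bound, assuming all 286 enter by the amendment and all are scanned exactly one month after allocation:

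- Stop arm: 143 × (1 − exp(−0.15/12)) = 143 × 1.24% = 1.8.
- Continue arm: 143 × (1 − exp(−0.075/12)) = 143 × 0.62% = 0.9.
- Total: about 2.7 of 57.

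The lower bound is 0. Reading the annual figures as proportions gives 143 × (0.648% + 1.345%), about 2.8 of 60, so the choice hardly matters.

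**5. PBD already present but unrecognised at entry.** This needs a time since last imaging, which the Protocol does not give. Assume 6 to 12 months, and that every amendment patient is scanned late.

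- At the full 7.5% per year: 1 − exp(−0.0375) = 3.7% to 1 − exp(−0.075) = 7.2%, or 5 to 10 of 143 patients and 11 to 21 of 286.
- Section 1.13 builds 7.5% from about 5% per year symptomatic disease. If symptomatic events are recognised clinically, 2.5% per year stays hidden: 1.2% to 2.5%, or 1.8 to 3.5 of 143 and 3.6 to 7.1 of 286.
- With no late scans the number affected is 0.

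**6. Standard route.** Section 1.7 lets year-2 imaging move by ±1 month. It lets randomisation move by ±1 month in one place and by −1 to +2 months in another. Imaging at +1 and randomisation at −1 puts the scan 2 months after allocation, against a year-two criterion in 1.6 that also refers to imaging before randomisation.

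**The case against.** **The counts are small and conditional.** This stands. Most amendment patients may be scanned in the two permitted months before entry. The larger figures in step 5 rest on an assumed imaging gap and on everyone being scanned late. Absorbed events would fall more in the stop arm (1.8 against 0.9), which pulls towards no difference.

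**A reader might infer that PBD on a late scan will be counted as an early event, or that the patient will be removed because of the arm.** The Protocol says neither. Under 1.5 such disease could equally become part of the baseline, and no rule covers removing ineligible patients after allocation. What can be said is that the handling is unstated. The discretionary exits in 1.12, including one specific to control-arm patients with PBD who restart treatment, leave room for arm-dependent choices.

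**A reader might infer that baseline markers are materially contaminated.** Section 1.7 bars sampling after an infusion in years 2 to 4 and keeps that visit plan for amendment patients. At most a stop-arm sample comes about two weeks later than it otherwise would. This part is minor.

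**The randomisation procedure in appendix 6 is not shown and may impose an order.** It may. But a site following the text of 1.7 complies while scanning after allocation, so the rule as stated still needs correcting.

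**Conclusion.** The point holds as a fault in the order of steps. For amendment patients the 1.7 window permits the only budgeted baseline scan to follow allocation. That conflicts with the pre-randomisation exclusion in 1.6 and the baseline at randomisation in 1.5, in an unblinded trial analysed per protocol.

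Its numerical size cannot be fixed from the Protocol. First-month events absorbed into baseline lie between 0 and about 2.7. Unrecognised PBD at entry depends on an assumed time since last imaging and is lower if symptomatic events are noticed clinically. The conclusion rests on the sequence and not on these counts. It is not a claim that power is lost, that selective exclusion has occurred, or that the sample size is wrong.

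**What to change.** For the amendment route, replace the 1.7 wording with: bone imaging within two months before randomisation and assessed for PBD before the patient is allocated; quality-of-life questionnaires and fasting bone markers completed before randomisation. Delete the three allowances for collection after inclusion on this route.

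For the standard route, state that year-2 imaging is done and assessed before randomisation, and reconcile the two randomisation windows in 1.7. Changing only the amendment route would leave the same gap open there.

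Cost: a short protocol amendment, with some patients randomised slightly later. No scan is added and the sample size stays at 143 per group. Around randomisation, the amendment-route window narrows from −2 to +1 months to −2 to 0. With the 2½-year scan at 5 to 7 months after randomisation, the interval from baseline to first follow-up changes from 4–9 to 5–9 months.
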